## Methods/Design

The CONsolidated Standards Of Reporting Trials (CONSORT) statement was followed to describe the design of this study. This checklist is used worldwide to improve the reporting of Randomized Controlled Trials (RCT) [24-26].

### Organization of the study

The design of the study is a multicentre prospective RCT in patients undergoing gynaecological surgery and will be conducted in the Netherlands. In this study, the intervention group will receive a multidisciplinary care program (e-health intervention, integrated care management & participatory workplace intervention) and will be compared with a control group that receives usual given peri-operative care together with a placebo e-health intervention. Figure 1 presents a brief outline of the design of the study.

**Figure 1 F1:**
[figure not shown]
**Design of the RCT**.

The seven participating hospitals in this study will be six general (teaching) hospitals and one University hospital, all localized in or nearby Amsterdam: 1)The Amstelland Hospital; 2)The Flevo Hospital; 3) The Kennemer Gasthuis; 4) The Onze Lieve Vrouwe Gasthuis; 5) The Sint Lucas Andreas Hospital; 6) The Spaarne Hospital and 7) The VU University Medical Center.

### Recruitment of patients

Participants for the study will be recruited from the waiting lists of participating hospitals. Patients scheduled for a hysterectomy or laparoscopic adnexal surgery because of benign disorders will receive an invitation letter on behalf of their gynaecologist, together with an information package consisting of: 1) patient information letter about the study, 2) Informed Consent (IC), 3) reply card to send to the researchers when not interested in participation in the study and finally, depending on the requirements of the particular hospital, 4) a leaflet about participating in scientific research in general.

When the researchers do not receive a reply card of the patient within two weeks after the delivery of the information package, they will make contact to evaluate whether she is interested in participation in the study. Phone numbers and addresses of these patients will be send to the researchers by the participating hospitals weekly. Patients willing to participate and meeting the inclusion criteria will be asked to return the signed IC and will receive the baseline questionnaire about four weeks before surgery. Subsequently, when both are filled out and the surgery is scheduled within four weeks, the patient will be randomized for the intervention or usual care group.

### Study population

Eligible patients for this study are women aged between 18-65 years, employed for at least 8 hours per week (paid or unpaid) and scheduled in one of the participating hospitals for a laparoscopic adnexal surgery and/or hysterectomy due to benign disorders. Exclusion criteria for this study are: 1) (suspicion of) malignancy; 2) (ectopic) pregnancy; 3) deep infiltrating endometriosis; 4) concomitant surgical procedures or major health problems/psychiatric disorders affecting recovery or daily activities; 5) being sick listed for more than 4 weeks, or when the surgery is to cure the reason of the absence of work, sick listed for more than 2 months; 6) working temporarily for an employment agency without detachment; 8) dealing with a lawsuit against their employer; 9) not able to understand or complete the questionnaires written in the Dutch language and 10) no access to internet.

### Randomization

To prevent unequal randomization between hospitals, patients will be pre-stratified by hospital and type of surgery (laparoscopic adnexal surgery, total laparoscopic-/laparoscopic assisted-, vaginal- and abdominal hysterectomy). A computer-generated block randomization will be performed on individual level. The blocks consist of four characters to ensure roughly equal group sizes with each stratum and are randomly varying in sequence. Randomization will be executed by an (independent) research assistant, after the patient has completed baseline measurements and IC.

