### Blinding

Patients will be blinded for the allocated treatment. Treatment allocation (randomization) will take place by computer-generated block randomization after completion of baseline questionnaire and IC. After randomization, all patients will receive access to the e-health intervention. However, after logging into the website with their personal login credentials, the kind of information provided by the e-health intervention will depend on the group the patient is randomized for.

During recruitment, the patients will be told that in case they do not RTW within 10 weeks after surgery, they might be approached for supplementary care depending on the care program they are randomized for. Nevertheless, explanation will only be given about the comparison of two different types of information supply and peri-operative guidance and not about the content of peri-operative guidance according to the 'intervention' or 'control' group.

Due to the different treatments in both groups, therapists and researchers cannot be blinded for the allocated treatment of the patient.

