The main limitation of this study is that contamination between the intervention and control group cannot completely be prevented, because the randomization will be performed on patient level. With regard to the health care providers, it is impossible to blind them for the intervention allocation, because the allocation determines the kind of convalescence recommendations that should be given to the patient. Therefore, it is important for them to follow and distinguish consequently the protocol belonging to the intervention versus the control group. Contamination may occur when care providers use acquired insights received through the convalescence recommendations for the intervention group to adapt their usual care and convalescence recommendations given to the control group. To minimize this effect, we will only proactively work on the familiarity of the protocols among the health care providers and not on the detailed contents of the convalescence recommendations for the patients in the intervention group. The patients' gynaecologists will only receive a summary of the guideline by means of their patients' record, in order to pass it on to the patient at discharge from the hospital. GPs and OPs will only receive the guideline when the patient hands over her tailored convalescence recommendations or work reintegration plan to them. A learning curve of the health care providers to flawlessly execute the protocol in the intervention group may be expected. This implementation curve may result in less effect of the intervention during the beginning of the study, which should receive attention during the analysis of the results. To accelerate the implementation of the protocol, pocket maps with the description of the intervention will be distributed, teaching meetings with the health care providers about the protocol will be organized and the protocol will be added to the medical file of the patient. Although therapists and researchers cannot be blinded for the allocated treatment of the patient, they will not be involved in measuring the outcomes, since all outcome measures are self-reported and the questionnaires will be sent by email or post to the patients. Therefore, it is unlikely that the way patients complete the questionnaires, will be influenced by the researcher and care providers. Moreover, the therapists of the multidisciplinary team (RTW-coordinator, OT, and other care providers), will not be involved in the assessment of the outcomes. With concern to contamination between patients of the intervention and control group, a chance meeting cannot be excluded. According to the protocol, patients from different groups should not be placed in the same hospital room, but it cannot be prevented that patients will meet outside the room. Another limitation of this study is the fact that the integrated care management and the workplace intervention will be carried out by one clinical occupational physician and OT, which might affect the execution of the intervention. However, both will work according to a detailed standardized protocol in order to minimize their personal influence on performance of the intervention as much as possible. Compliance to e-health interventions is sometimes low. We tried to minimize the risk of low compliance as much as possible by spending extra effort and time on involving the stakeholders (end-users) in the development of this intervention and adapting it to their specific needs by use of the intervention mapping protocol [22]. Finally, although the participating hospitals reflect the proportion of (non) university hospitals in the Netherlands, they are all located in the urban agglomeration in the Western part of the Netherlands, which might be of influence on the educational level of the patient population. Because research has shown that both living in the city as well as higher educational level are associated with more frequent use of the internet for health or illness matters, it should be determined whether the educational level and internet use of the participating patients reflects that of the general Dutch population, before the results of this study can be interpreted as representative of all gynaecological patients in the Netherlands [59].

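### Block length is fixed at four while the recruiting researchers are unblinded; randomly varied, undisclosed lengths would be a minor, low-cost improvement to concealment

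*Protocol article*

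**What the plan says.** All references are to the protocol article.

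- **Randomization:** "patients will be pre-stratified by hospital and type of surgery", with four surgery categories listed. On the blocks: "The blocks consist of four characters to ensure roughly equal group sizes with each stratum and are randomly varying in sequence". The varying sequence is the order of the four assignments; one length is given. An independent research assistant carries out the randomization once consent and baseline measurements are complete.
- **Organization of the study (text under Figure 1):** "The seven participating hospitals in this study will be six general (teaching) hospitals and one University hospital". Seven hospitals by four surgery types gives 28 strata.
- **Recruitment of patients:** hospitals pass contact details to the researchers weekly. Where no refusal card arrives within two weeks, "they will make contact to evaluate whether she is interested in participation in the study". Willing women who meet the criteria then return consent and the baseline questionnaire, and are randomized when surgery is due within four weeks.
- **Blinding:** patients are described as blinded, but "therapists and researchers cannot be blinded for the allocated treatment of the patient".
- **Strengths and limitations:** of the care providers, "it is impossible to blind them for the intervention allocation, because the allocation determines the kind of convalescence recommendations". The same section says that every waiting-list patient is invited.

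**The concern.** Concealment has two parts. Nobody who enrols should be able to see the list, and nobody who enrols should be able to work out the next entry. The independent assistant secures the first part. The second depends on how much past allocations reveal, and with a single short block length they reveal a good deal: once one arm has used its two places in a block, the rest of that block is known.

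The people placed to use this are the recruiting researchers. They make the contact, apply the criteria and know past allocations. Most exclusions are factual, but item 4 under Study population (other major health or psychiatric problems that bear on recovery or daily activities) needs judgement and is tied to prognosis for return to work. If the likely next arm coloured that judgement, or how actively a hesitant woman was encouraged, the arms could differ in prognosis from the start. The article's claim that selection rests only on clearly defined criteria is easier to defend when the next assignment is hard to predict.

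**Working it through.** **Inputs.** Block length 4, stratification by hospital and surgery type, 7 hospitals and 4 surgery types (Randomization; Organization of the study). Planned size: 191 before dropout and 212 after (Sample size; 191/0.9 = 212.2). The article gives no figure for predictability, so there is none to reproduce. *Assumption:* each block holds two assignments per arm; the text says only "to ensure roughly equal group sizes with each stratum".

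**Complete blocks.** There are 6 equally likely orders of AABB.
- Positions 1 and 2 are never certain.
- Position 3 is certain only if the first two match: 2 of 6 orders = 1/3.
- Position 4 is always certain.
- Certain share = (0 + 0 + 1/3 + 1)/4 = 33.3%.
- Best-guess hit rate = (1/2 + 2/3 + 2/3 + 1)/4 = 70.8%, against 50% for pure chance. At position 2 the opposite arm has probability 2/3. At position 3 the guess is certain with probability 1/3 and even otherwise: 1/3 × 1 + 2/3 × 1/2 = 2/3.

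**Incomplete last blocks.** A stratum of n women has (4/3) × floor(n/4) certain assignments, plus 1/3 if three women are left over.
- n = 8: 2 × 4/3 = 2.667. n = 7: 4/3 + 1/3 = 1.667.
- 212 women spread exactly evenly over 28 strata: 16 strata of 8 and 12 of 7. Then 16 × 2.667 + 12 × 1.667 = 62.7, and 62.7/212 = 29.6%.

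With random stratum totals (simulation means, equal or unequal expected stratum sizes):

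| Women | Strata | Equal | Unequal |
|---|---|---|---|
| 212 | 28 | 27.8% | 28.3% |
| 212 | 35 | 26.5% | 27.2% |
| 191 | 28 | 27.2% | 27.8% |
| 191 | 35 | 25.7% | 26.6% |

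The 35-stratum rows apply if total laparoscopic and laparoscopic-assisted hysterectomy are kept separate. An exactly even split over 35 strata is an unfavourable corner case (33 strata of 6, 2 of 7): 33 × 1.333 + 2 × 1.667 = 47.3, or 22.3%. For about 28 strata the range is 27% to 30%; over all simulated settings the means run from about 26%.

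**With varied lengths.** These are exact probabilities for an observer who knows which lengths are possible (equally likely) but not the length of the current block:

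| Lengths | Certain, n = 6 | n = 8 | n = 12 | Best guess, n = 6 | n = 8 | n = 12 |
|---|---|---|---|---|---|---|
| 4 only | 22.2% | 33.3% | 33.3% | 66.7% | 70.8% | 70.8% |
| 4, 6 | 7.5% | 5.9% | 6.3% | 67.2% | 66.8% | 68.0% |
| 2, 4, 6 | 3.0% | 3.0% | 3.4% | 68.6% | 68.6% | 69.3% |

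The gain lies in removing certainty. The hit rate of an informed guess falls by only 2 to 4 percentage points in a stratum of 8, and not at all in a stratum of 6.

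**The case against.** The safeguards are real. Consent, baseline data and eligibility all come before allocation by an independent assistant, and all waiting-list patients receive a letter. A woman's place in her block also depends on when she returns her documents and when surgery is scheduled. So a recruiter on the telephone often cannot know which position she will take, and the computed share describes knowledge just before assignment, not at the call. The recruiters serve all seven hospitals and would have to keep about 28 tallies. The article does not say that they know the block length; a condensed article may leave that to the full protocol, so its silence is not counted here. Short blocks also serve a stated aim, balance in small strata. All of this stands and keeps the point minor. It does not show that a single fixed length is needed: the aim is only rough balance, and mixed lengths still bound the imbalance.

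Several stronger readings are tempting but not supported:
- *That this is an open trial.* The Blinding section describes patients as blinded, the control arm has a placebo website, and outcomes are self-reported without therapists or researchers measuring them. Only researchers and care providers are unblinded.
- *That a prediction could decide who is invited.* Invitation goes to everyone on the waiting lists. Any discretion lies later, at the call and the eligibility judgement.
- *That only four strata need be followed.* This would fit staff within one hospital. Of care providers the article does say "it is impossible to blind them for the intervention allocation", but it does not describe them as enrolling patients.
- *That any resulting bias would be beyond repair.* The plan measures prior sick leave, work factors and expectations about return to work, and allows adjustment for prognostic differences. Selection on measured factors could be partly addressed; selection on unmeasured ones could not.

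**Conclusion.** The point holds as a minor, low-cost improvement. With one block length of four, a recruiter who knew the length and tracked allocations by stratum could foresee roughly 26% to 30% of assignments with certainty, and one third within complete blocks. This rests on 2:2 blocks, about 28 strata, known block length, tallies kept by stratum, and knowledge of the woman's place in the sequence. It measures an opportunity; nothing in the article shows that selection occurs. The existing safeguards narrow that opportunity without closing it, because the people who make the contact and apply the criteria also know past allocations.

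**What to change.** Generate each stratum's list with block lengths that vary at random, for example 4 and 6, or 2, 4 and 6. Do not disclose the lengths to the recruiting researchers or hospital staff. If recruitment has begun, replace only the unused parts of the lists. The independent assistant and the order of consent, baseline and randomization can stay as they are.

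The cost is regenerating computer lists, with no added sample size, staff or visits. The downside is that imbalance within a stratum can reach 3 instead of 2, since half of a block of 6 is 3 and half of a block of 4 is 2. That is still compatible with the stated aim of roughly equal groups.

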### Control group; placebo e-health intervention and usual peri-operative care

In the Netherlands, there is a considerable variation in given peri-operative care and convalescence recommendations for gynaecological patients. The number of consultations and also the available time for counselling differs per hospital. After discharge, in general the patient receives one appointment for a post-operative check-up in an outpatients' department for about six weeks after surgery. Other medical care by gynaecologists and GPs is given only on demand. Patients with paid work who do not RTW within six weeks after surgery, are generally consulted by their OPs due to Dutch legislation.

In addition to given usual care, patients in the control group of this RCT will get access to a placebo e-health intervention. This website has five unique pages and provides the patient with a patient leaflet and telephone numbers of the participating hospitals. The patient leaflet is derived from The Dutch Society of Obstetrics and Gynaecology (NVOG) website and forms the basis of almost all leaflets provided in Dutch hospitals for hysterectomy or laparoscopic adnexal surgery on benign indication [27,28].

### Intervention group; multidisciplinary peri-operative care program

Patients in the intervention group, receive normal usual peri-operative care with the adjustment that the care providers supply standardized detailed convalescence recommendations to the patients [18]. In addition, this group will get access to an e-health intervention and, when they have not returned to work completely within ten weeks after surgery, supplementary care of a clinical occupational physician and (if relevant) a workplace intervention by an Occupational Therapist (OT) will be offered. This stepped care approach of additional care will be described in detail below.

#### Step 1: all patients get access to an e-health intervention from four weeks before surgery

To improve peri-operative gynaecological care, an interactive e-health intervention aiming at the empowerment of gynaecological patients during the peri-operative period including return to normal activities and work was developed [17]. This e-health intervention targets at behaviours of patients as well as of gynaecologists, GPs, OPs, employers and family members. It provides tools to compose detailed tailored instructions on the resumption of (work) activities, based on the operation date and how the surgery went (input of gynaecologist). These recommendations are based on a Delphi study among gynaecologists, GPs and OPs, using a structural consensus method including a systematic review of available literature [18]. The e-health intervention additionally provides tools (e.g. a video) to improve the communication between patients, care-providers and employers, to prevent conflicting recommendations and stimulate patients and employers to discuss potential RTW problems and to develop a work reintegration plan. Furthermore, general information on the surgical procedure itself, the (possible) consequences of the surgery and clear instructions about which symptoms require additional consultation of care providers or adaptation of convalescence recommendations, is available by the e-health intervention. In addition, it supplies an extensive list of frequently asked questions and a forum to contact other patients. Finally, patients' recovery can closely be monitored by the website, allowing the e-health intervention to advise the patient to contact a clinical occupational physician for support with reintegration when she has not RTW ten weeks after surgery. Table 1 presents an overview of the various tools of this e-health intervention.

**Table 1 T1:** Structure of the e-health intervention [17]

Tool	Content	Involved stakeholders
1. Compose a work reintegration plan	■ Tool to compose a detailed reintegration plan with adaptations for work if necessary.	➢ Patient, Employer, OP
2. Resume normal activities	■ Tool to compose detailed advice about when normal (private) activities can be carried out again	➢ Patient, family
3. Evaluate complications	■ Estimate severity and consequences of a complication	➢ Patient, gynaecologist
4. Recovery Monitor	■ Monitoring recovery and offering assistance when relevant	➢ Patient
5. Satisfaction with recommendations	■ Evaluation and explanation of convalescence recommendations	➢ Patient
6. Satisfaction with the recovery process	■ Evaluation of satisfaction with recovery and reintegration process. Provision of advice regarding which care provider(s) to approach to receive appropriate help, when relevant.	➢ Patient
7. Invite Employer	■ Invite employer for (anonymous) section of the website which includes video (see below) and recommendations	➢ Patient, Employer
8. Video	■ Illustrate common pitfalls during the peri-operative and reintegration period	➢ Patient, employer, gynaecologist
9. Recommendations for employee	■ Advice for a successful reintegration	➢ Patient
10. Recommendations for employer	■ Advice for appropriate involvement regarding employee during the peri-operative and reintegration period	➢ Employer
11. Frequently asked questions	■ Extensive list of answers and pictures to most frequently asked questions	➢ Patient
12. Glossary	■ Explanation of most frequently used medical terms	➢ Patient
13. Forum	■ Ability to interact in public or through private messages with other patients	➢ Patient
14. Links to other websites	■ Relevant websites concerning the peri-operative and reintegration period	➢ Patient
15. Guidelines	■ Well-defined convalescence recommendations after hysterectomy and laparoscopic adnexal surgery	➢ Gynaecologists

Structure of the e-health intervention to empower gynaecological patients during the peri-operative period, including return to normal activities and work

#### Step 2: if sick leave exceeds ten weeks, additional integrated care management including workplace intervention will be offered

This part of the intervention will only be offered to the patient when she is not fully returned to work ten weeks after surgery and consists of two main protocols; 1) Integrated care protocol and 2) Workplace intervention protocol and is based on a previous study of patients with chronic low back pain [23].

